**v: Measurements:**

**Height and Weight.** Body weight will be measured via a Tanita scale after voiding. Participants will wear t-shirts, shorts and no shoes during measurement. Height will be measured using a stadiometer. BMI percentile will be calculated based upon growth curves for each participant’s age and gender (Kuczmarski et al., 2000).

**Active Video Game (AVG) Reinforcement Task.** Participants will be given a list with 4 AVGs and 4 age-appropriate sedentary video games. Participants will sample and then rate their liking for each game on a scale of 1-10, with greater scores indicating a greater preference for that game. The highest liked active and sedentary videogames will be made available during the testing session. Participants will then play a slot-machine style game in which mouse clicks earn them time towards their most-liked game. Two computers will be set up, one for sedentary and one for active video games. Participants will be permitted to move freely between the computers.

During the game, three shapes of different colors will appear upon the screen. The participant will click upon the shapes in an attempt to make the shapes/colors match. Each match will earn one point, with 5 points earned at a particular schedule translating to minutes in each activity (in five minute intervals). Participants will be permitted to earn as much time with each game as they choose. The RRV of each game will be assessed by total responses and by maximum level completed (Pmax) which a participant is willing to make in order to earn minutes of play in their desired activity. Reinforcing value is measured using progressive ratio schedules of reinforcement. At first, points are delivered after every 4 presses, but then the schedule of reinforcement doubles (4, 8, 16, 32, […] 1024) each time 5 points are earned.

Participants will be permitted to earn points until they have accumulated the time they wish or they no longer wish to engage in the task. Before commencement of the task, the researcher will explain the task and demonstrate with a practice round. The participant will complete the task alone with the researcher monitoring their progress via computer and audio feed in an adjacent room. After task completion, the participant will be permitted to complete the AVGs and/or sedentary video game with the participant playing against the game rather than against an opponent. While the child is completing the AVG reinforcement task, the parent will waiting in an adjacent room, to avoid influencing the child’s responses.

**Physical Activity (PA) Reinforcement Task.** The physical activity reinforcement task will follow a schedule identical to the AVG reinforcement task. The task will also follow a procedure identical to the AVG reinforcement task, with the exception that the two workstations will allow the participant to earn time towards either AVGs or a traditional game/sport. The AVG and traditional sport/games will be supervised by a researcher and will include games comparable to the AVG games. The traditional active game will be completed indoors at the Choice Fitness Center. Children will have the options of playing traditional games/activities such as hockey (with a puck, stick and net), soccer (with a ball, cones, and net), racquetball (with a racquet and ball), and basketball (with a ball and net).

**Usual Physical activity.** PA will be assessed with the ActiGraph WGT3X-BT monitor. The device has a 3-axis accelerometer to collect measures of raw acceleration, and PA amount and intensity, and sedentary time. The ActiGraph has been extensively used in research studies and validated for use in children ages 8-12 (Ekelund et al., 2001; Puyau, 2002; Trost et al., 1998) Children will be instructed to put the ActiGraph on upon waking and only take it off while sleeping or in water-based activities. Parents will be trained regarding the importance that their child wears the ActiGraph at least 10 hours/day (standard to ensure validity) including the times that they play AVG for 7 consecutive days during the indicated study periods. Parents will receive written instructions on use, including appropriate care and placement on the right iliac crest (a belt is provided) (Appendix 18) (Patterson et al., 1993). The ActiGraph will be initialized for 5 second epochs and the data downloaded using the ActiLife software and stored in a “dat” file. Then, a customized Systat code will be used to identify spurious data of >16,000-20,000 counts, negative counts, and strings of identical counts. It will score sequences of 20 + minutes of consecutive zero counts as non-wear time. The total amount of PA from the activity monitor will be expressed as the average of total counts per minute of time worn. The main outcome variables will be mean counts/minute an index of mean total PA and time spent in moderate to vigorous PA (MVPA). The ActiGraph data will be converted to 15-sec epochs and MVPA determined using the count thresholds developed by Evenson et al. (2008; Trost et al., 2011).

**Physical Activity Mode and Sedentary Activity.** Physical activity and sedentary activities will be primarily assessed using the accelerometers. However, accelerometers do not provide detail of the mode of physical activity or sedentary behavior. As an adjunct, children will complete a 24 hour recall based upon the procedures described in Simons and colleagues (2015). Children will be asked to indicate for three time periods (awakening to noon, noon to 4 PM, and 4 PM until bedtime) how much time they had spent in a predetermined list of activities including active video games, sedentary video games, other screen-based sedentary activities (TV, computer, IPad), non-screen based sedentary activities (homework, music/art lessons), physical activity (sports, physical education classes), and other physical activity (chores, walking to school) (see Appendix 4). Categories will be slightly modified from the original study to make them age-appropriate. Participants will complete the recall on 4 days, including two school-days and two weekend days. The participating parent will be sent text and/or email links to the recall on Survey Monkey, so that they may fill out the recall at the end of each day. Parents will be encouraged to work with their child to complete the recall.

**Beverage and Snack Consumption.** To measure non-meal snacking during playtime or games, children will be administered the Beverage and Snack Questionnaire (BSQ) (Neuhouser et al., 2009). This tool consists of 19 questions designed to measure consumption of common sugar-sweetened beverages and snack foods, both in school and at home. The tool was designed for school-aged children (mean age = 12.7). Validation studies have found this measure to have good reliability and validity (Neuhouser et al., 2009) (see Appendix 9).

***Mediators and Moderators***

**Exercise Self-Efficacy.** Self-efficacy will be measured using the *Children’s Self-Perceptions of Adequacy in and Predilection of Physical Activity Scale (CSAPPA)*. This scale measures child’s beliefs about their ability to perform well in physical activities such as physical education classes and sports teams (adequacy), their likelihood to choose physical activity over a sedentary activity (predilection), and enjoyment of physical activity. The scale consists of 20 items which children rate as “really true for me” or “sort of true for me” (Hayes, 1992). The scale was designed for use with children ages 8-16 and has been successfully used experiments with similar age groups (Roemmich et al., 2012). The scale has been shown to have adequate test-retest reliability as well as predictive validity (Hayes, 1992) (see Appendix 5).

**Motivation for Exercise.** Intrinsic and extrinsic motivation for exercise will be measured with the *Behavioral Regulations in Exercise Questionnaire, 2^nd^ edition* (BREQ-2). The original BREQ was developed as a measure the self-determination theory’s continuum of external vs. internal motivation for exercise (Mullan, Markland & Ingledew, 1997). The original version was developed for use with adults and examined four subscales: external regulation, introjected regulation, identified regulation and intrinsic regulation. The BREQ-2 includes an additional subscale measuring Amotivation (Wilson et al., 2006). The BREQ has good psychometric properties with children ages 7-11 (Sebire et al., 2013) and the BREQ-2 has been utilized successfully with children ages 8-11 years (Saavedra et al., 2014). The questions may be slightly modified to make them more easily comprehensible to children (see Appendix 6).

**Motivation for Active Video Games (AVGs).** Questions from the BREQ-2 (Wilson et al., 2006) will be modified so that the question refers to motivation towards AVGs rather than physical activity. While not specifically designed for alternate behaviors, variations of the BREQ-2 have been successfully used to measure motivations for non-exercise behaviors such as children’s oral health (Toutouni et al., 2014). As validation, this measure will be examined for internal validity via Cronbach’s alpha and criterion validity via correlations with RRV_video games_ and minutes spent playing AVGs (see Appendix 7).

**Motivation for Sedentary Behavior**. Questions from the BREQ-2 (Wilson et al., 2006) will be modified so that the question refers to motivation towards sedentary behavior (non-active video games, television, computers etc.) rather than physical activity. Similar to motivation for AVGs, this questionnaire will be validated via Cronbach’s alpha, RRV correlations, and minutes spent in sedentary activity (see Appendix 8).

**Physical activity-related parenting behaviors.** Parents will fill in The Activity Support Scale for Multiple Groups (ACTS-MG) developed by Davison (2011). The ASSMG includes 12 items, 3 each in: Logistic Support (parents making provisions enabling their child to be physically active), Explicit Modeling (parents using their own behavior to encourage their child to be active), Use of Community Resources (make use of community resources to get their child to be active) and Restricting Access to Sedentary Activities. Cronbach’s alpha ranges from 0.69 to 0.88. Items are measured on a 4 point scale (0 = strongly disagree; 4= strongly agree) with higher scores showing greater parental support for physical activity. The scale has good overall factorial validity and internal consistency (Davidson et al., 2011) (see Appendix 10).

**Parent self-efficacy for exercise.** The Barriers Self-efficacy Scale (BARSE) (McAuley, 1992). For the BARSE they rate how confident they are that they could motivate themselves to exercise regularly, for at least three months, despite common barriers. The scale consists of 13 items measured on as 10 point percentages (0 = not at all confident; 100 = highly confident). Items are summed with higher scores indicating greater self-efficacy. Scores predict exercise behavior (McAuley, 1991). The scale has good internal consistency and validity (McAuley et al., 2010) (see Appendix 11).

**D. Statistical Analysis Plan**

*Power analysis and sample size:*

Prior research has shown an effect size of approximately eta squared (h^2^) = 0.45 and a mean difference between high (M = 41.4) vs low autonomy (M = 22.5 minutes of play) conditions (difference = 18.9 minutes) (Roemmich et al., 2012). Based upon these and conservative estimates from Cohen’s guidelines for multivariate effects (Cohen, 1992), estimates of required sample size to achieve power exceeding the 1 - β = .90 level were run and a sample size of N = 25 participants per autonomy condition was recommended.

Independent variables will be the study condition of high vs. low autonomy (categorical variable) and time (categorical). Dependent variables will consist of total scores in RRV_video games,_ total scores in RRV_active games_, total weekly minutes of physical activity, total weekly minutes of AVG play, total weekly minutes of sedentary video game play, total weekly minutes of other screen-based sedentary activity, total weekly minutes of non-screen based sedentary activities, maximum level completed towards AVGs, maximum level completed towards sedentary video games, BMI/ weight loss, total energy expenditure, exercise self-efficacy, intrinsic motivation towards AVGs, intrinsic motivation towards exercise, intrinsic motivation towards sedentary video games, sweetened beverage/snack consumption (continuous variables). Participant exercise self-efficacy, parental exercise self-efficacy, and parental support for physical activity will be treated as moderating covariates (continuous).

*Preliminary Analyses:*

Preliminary data analysis will consist of all continuous data being examined for normality assumptions (skew, kurtosis, linearity, homogeneity of variance). Demographics will be tallied and basic descriptives including mean, median, maximum and minimum scores, and standard deviations calculated. For categorical variables, frequencies will be run. While significant attrition is not anticipated, participants failing to provide complete data will be compared to participants providing complete data in terms of baseline measures of age, gender, ethnicity, study condition, and baseline RRV of the key dependent variables via ANOVA tests for continuous variables and chi-square tests for categorical variables. Similar comparisons of baseline variables will be used to compare the high vs low autonomy groups to ensure that all possible confounds are evenly distributed at baseline. No significant differences between groups are anticipated. Bivariate correlations will also be run between the main study variables, both at baseline and at post-assessment. For each of the main questionnaires, internal validity of each total scale and subscale will be measured via Cronbach’s alpha.

*Major Analyses:*

Major analyses for Hypothesis 1 will take initially the form of a repeated measures analysis of covariance (ANCOVA). The between-subjects grouping variable will be high vs low autonomy. Outcome variables will take the form of means and standard deviations with 95% confidence intervals. Baseline variables, age, gender, and baseline enjoyment of AVGS will be included as control variables/ possible moderators. Moderating variables will include participant’s exercise self-efficacy, parental support for physical activity, and parental exercise self-efficacy. Moderating variables will be run separately. Each dependent variable shall be run separately.

Major analyses for Hypothesis 2 will take the form of multilevel regression equations. The main independent variable will be the changes in total reinforcement value (Pmax) of AVGs. Covariates will include age, gender, baseline enjoyment of sedentary video games, baseline time spent playing sedentary video games and other screen-based activities. The primary outcome variables will be maximum level earned (Pmax) towards sedentary video games and minutes of sedentary video games played per week. Once again, results will be considered statistically significant at α = .05. Covariates will be considered statistically significant as evidenced by significant β coefficients and significant increases in R^2^ values. Categorical covariates will be dummy-coded according to the procedure outlined in Cohen et al. (2003).

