**B. Overall Objective and Specific Hypotheses to be tested**

The goal is to investigate how autonomy might be used to increase children’s intrinsic motivation towards active video games, active play, and/or sedentary activity. Specific hypotheses include:

**H1a (Primary):** High autonomy of AVG play will result in increased reinforcing value of AVGs relative to sedentary video games. Lower autonomy of AVG play will not show an increased reinforcing value of AVG relative to sedentary video games.

**H1b**: High autonomy of AVG play will increase intrinsic motivation to play AVGs relative to low-autonomy control condition.

**H1c:** High autonomy of AVG play will increase intrinsic motivation to engage in physical activity relative to low-autonomy control condition.

**H1d:** High autonomy of AVG play will result in more hours of AVG play during the follow-up phase relative to the low-autonomy control condition.

**H1e:** High autonomy of AVG play will increase usual physical activity during the follow-up phase relative to the low-autonomy control condition.

**H1f:** High autonomy of AVG play will result in increased reinforcing value of AVGs relative to traditional active games.

**H2a:** Increased reinforcing value of AVGs will result in increased reinforcing value of sedentary video games.

**H2b:** Increased reinforcing value of AVGs will result in increased hours/week spent playing sedentary video games.

**H2c**: Increased reinforcing value of AVGs will result in increased time spent in other screen-based sedentary activities (television, computer games, tablets/cell phones).

**H2d:** Increased time spent in screen-based sedentary activities will result in increased sweetened beverage/snack consumption.

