**ii. Design:**

The overall design will be a 2 group factorial design with autonomy condition treated as a between subject variable (high autonomy, low autonomy). Participants will be randomly assigned to a high autonomy group or a low-autonomy group. Time (baseline, end of 6 week intervention, 4 week follow-up) will be treated as a within-subject variable. Participants will be blocked according to Taves minimization on gender (male vs female), BMI (above 85^th^ percentile vs. below 85^th^ percentile), and baseline liking of AVG (7 and lower vs. 8-10 on 10 point Likert scale).

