*Baseline RRV Assessments:* RRV assessments will take place in the Grand Forks Human Nutrition Research Center (GFHNRC) laboratory space at Choice Health and Fitness Center. On separate days children will be assessed for their relative reinforcing value of active to sedentary video games (RRV_video games_) and RRV of active video games to traditional active games (RRV_active games_). Order of these tests will be counterbalanced among participants. Participants will be asked to sample and rate their liking of four active video games (Appendix 12), four inactive video games (Appendix 13), and four traditional games/sports (Appendix 14). Children will be permitted to briefly sample games with which they are not familiar. Following the RRV task, children will be permitted to play the games corresponding to time earned on the task. Active and sedentary video games shall be played at Choice Health and Fitness spaces. Participants and their parent will complete a 24 hour recall assessing baseline time spent in physical activity, sedentary video games, and other screen-based sedentary activities at the end of one of these visits. Parents and children will complete the 3^rd^ and 4^th^ of the 4 recalls during weekend days at home using SurveyMonkey.

*Week 1 and 3 Assessments:* Children will wear an activity monitor for 7 consecutive days in the same manner as at baseline assessment. Participating parents and children will also be asked to fill-out the 24 hour activity recall on 4 days, including at least one weekend day.

*End of-intervention (Week 6) Assessments:* Outcome assessments will take place during and just after the last week of the 6 week intervention. Post-intervention anthropometry, questionnaire, RRV, and physical activity testing will be identical to screening/baseline assessments.

*4 Week (Week 10) Post-Intervention Follow-up Assessments and Debriefing:* At 4 weeks following the end of the intervention, participants will complete their final assessment, to determine whether intervention effects on videogame reinforcement, AVG use, physical activity reinforcement, physical activity, and sedentary behavior have been maintained for at least 4 weeks. The assessments will be identical to screening/baseline. Following the assessment, participants will be debriefed, asked for intervention feedback (Appendix 15 & 16), thanked for their time, and compensated.

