**Table 1. Testing Schedule**

|  | Screen | Baseline | Wk 1 | Wk 3 | End-Intervention  (Wk 6) | Follow-up  (Wk 10) |
| --- | --- | --- | --- | --- | --- | --- |
| Height | X |  |  |  | X | X |
| Weight | X |  |  |  | X | X |
| Demographic Questionnaires | X |  |  |  |  |  |
| PA/Sed Questionnaires | X | X | X | X | X | X |
| BSQ |  | X | X | X | X | X |
| RRV_video games_ |  | X |  |  | X | X |
| RRV_active games_ |  | X |  |  | X | X |
| Physical activity monitor |  | X | X | X | X | X |
| Debriefing |  |  |  |  |  | X |

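### Repeated measures ANCOVA for Hypothesis 1 keeps only children seen at all three times; a mixed model would keep partly observed children and reduce the loss

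*Protocol*

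**What the plan says.** Section D of the protocol (Major Analyses) states: "Major analyses for Hypothesis 1 will take initially the form of a repeated measures analysis of covariance (ANCOVA"). Each dependent variable is analysed separately. Section C.ii (Design) fixes the repeated factor: "Time (baseline, end of 6 week intervention, 4 week follow-up) will be treated as a within-subject variable".

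On incomplete children, section D (Preliminary Analyses) begins "While significant attrition is not anticipated" and then says only that "participants failing to provide complete data will be compared to participants providing complete data" on baseline measures and study condition. The sample size of 25 per condition shows no allowance for loss.

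The primary outcome is scheduled three times in Table 1: "RRV_video games_ | | X | | | X | X". Activity data are collected more often. Of weeks 1 and 3, section C.iii says "Children will wear an activity monitor for 7 consecutive days in the same manner as at baseline assessment", and Table 1 also places the recalls and the Beverage and Snack Questionnaire (BSQ) at those weeks. Hypothesis 2 is analysed differently, by multilevel regression.

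**The concern.** Classical repeated measures ANCOVA works on one complete row per child. If one of the three occasions is missing for an outcome, the whole row goes, including values already collected. For the primary outcome these come from laboratory visits at weeks 6 and 10, so a missed visit is easy to imagine in a ten-week trial in children. Section G already provides pro-rated payment for those who do not finish.

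Two things are at stake. The first is precision: with 25 per arm, each discarded child costs noticeable power. The second is bias: complete children are no longer the randomised groups, and the low-autonomy condition is the one expected to motivate less, so loss could differ by arm. Comparing completers with non-completers may reveal this but leaves the estimate unchanged.

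A separate, smaller matter is that the three-level time factor gives the week 1 and week 3 data no place in the Hypothesis 1 analysis.

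**Working it through.** **The plan's own figure.** Section D gives 25 per arm for power above 0.90. It cites eta squared 0.45, which is d = 2 × √(0.45/0.55) = 1.81, and then refers to conservative guideline values without saying which. With d = 1.81 a two-sided comparison needs 7 (normal) or 8 (t) per arm; with d = 0.8 it needs 33 or 34. Other variants with assumed correlations land near 25. The figure can be neither confirmed nor called wrong, so the check takes the effect that gives exactly 90% power with 25 complete children per arm.

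**Inputs.** From the protocol: 25 per arm, three occasions, α = 0.05. Assumed: two-sided test; baseline always observed; equal correlation 0.5 between occasions; each post-baseline visit missed independently with probability m.

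**Power formula.** Power = Φ(3.2415 × √(n_eff/25) − 1.960), where 3.2415 = 1.960 + 1.2816.

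**Complete cases.** The share kept is (1 − m)². For m = 0.10 it is 0.81, so n_eff = 25 × 0.81 = 20.25 and power = Φ(3.2415 × 0.9 − 1.960) = Φ(0.957) = 83.1%.

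**Mixed model.** Given baseline, the two later values have variance 1 − 0.5² = 0.75 and covariance 0.5 − 0.5² = 0.25, so their correlation is 1/3. For m = 0.10, 0.81 of children have both visits and 0.09 have each visit alone. In units of one fully observed arm:

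- diagonal information a = 0.81/(1 − 1/9) + 0.09 = 1.00125
- off-diagonal b = −0.81 × (1/3)/(1 − 1/9) = −0.30375
- information on the week 10 difference = a − b²/a = 0.909
- n_eff = 25 × 0.909 = 22.7; power = Φ(3.2415 × 0.9535 − 1.960) = 87.1%

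By symmetry the week 6 difference has the same figures.

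| Missed per visit (assumed) | Complete per arm | Power, complete cases | Effective n per arm, mixed model | Power, mixed model |
|---|---|---|---|---|
| 0% | 25.0 | 90.0% | 25.0 | 90.0% |
| 5% | 22.6 | 86.9% | 23.9 | 88.6% |
| 10% | 20.25 | 83.1% | 22.7 | 87.1% |
| 15% | 18.1 | 78.7% | 21.6 | 85.3% |
| 20% | 16.0 | 73.7% | 20.4 | 83.3% |

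With correlations of 0.3 to 0.7, the mixed model gives 86.9% to 87.3% at 10% missed and 82.9% to 83.6% at 20%.

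**Weeks 1 and 3.** For outcomes also measured at these weeks, a five-occasion mixed model gives 88.8%, 87.4%, 85.8% and 83.9% at 5%, 10%, 15% and 20% missed. The gain over three occasions at week 10 is at most 0.9 points across correlations 0.3 to 0.7. Only if the target were the mean over all post-baseline visits would these weeks matter much. At correlation 0.5, the variance of that mean given baseline falls from (1 + 0.5)/2 − 0.25 = 0.50 with two visits to (1 + 1.5)/4 − 0.25 = 0.375 with four, a drop of 25%. H1d and H1e do not ask that question; H1e, for example, reads "High autonomy of AVG play will increase usual physical activity during the follow-up phase relative to the low-autonomy control condition".

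**The case against.** The strongest reply is that the deletion is inferred. The protocol never says that incomplete children are excluded; the quoted sentence only describes a baseline comparison, and a separate statistical analysis plan, not shown, may set the handling of missing data. That is right as far as it goes. A reader might infer a stated exclusion rule, and the documents do not contain one. But the protocol does choose the model, and the point is about that choice. The word *initially* leaves room for another analysis but names none.

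A reader might also infer that ANCOVA is what shuts out weeks 1 and 3, so that changing the model would recover them. It would not. ANCOVA could take five levels, and a mixed model on the same three would omit the same weeks; the limit lies in the Design sentence. Nor does it touch the primary outcome, which is not measured then. Quoting the size of the unused data is also unsafe: Table 1 implies 5 × 7 = 35 monitor days but Table 2 lists 21, and Table 2 lists 20 recalls but the budget in Table 3 lists 16.

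Third, the size depends on assumptions. If the same 10% of children miss both visits, both methods keep 22.5 per arm and power is Φ(3.2415 × √0.9 − 1.960) = 86.8% either way. At the cited eta squared of 0.45, a fall to 20 per arm would cost almost nothing. Both remarks stand. They show that the gain may be small, but they give no reason to keep the method that discards data.

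Finally, a mixed model is not a cure. If children leave for unmeasured reasons linked to their outcome, it is biased too.

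**Conclusion.** The point holds for Hypothesis 1, including H1a. The named method in its classical form drops, outcome by outcome, any child missing week 6 or week 10, and the completer comparison does not make up for it. Like for like, a mixed model recovers about 4 power points at 10% missed per visit (83.1% to 87.1%), under 2 at 5%, and nearly 10 at 20%. It recovers nothing if no visit is missed or if the same children miss both.

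These figures rest on an assumed missed-visit rate, independent misses, an assumed correlation and an effect scaled to 90% power; the protocol states none of them. The mixed model reduces the loss, and it protects against bias only under missing at random.

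The documents do not support the stronger readings that the trial is shown to be underpowered, or that a change of model would remove the loss. The week 1 and week 3 matter is secondary: no effect on the reinforcement outcomes, and under one power point for the week 10 contrasts of H1d and H1e.

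**What to change.** In section D, for Hypothesis 1, replace repeated measures ANCOVA with a linear mixed model fitted by REML with a small-sample degrees-of-freedom correction. Include arm, visit, arm-by-visit, the baseline value of the outcome and the three minimisation factors (gender, BMI group, baseline liking of active video games). Baseline then enters as a covariate and not also as a level of visit. Analyse all children as randomised who have any post-baseline value, and state the missing-at-random assumption. Keep the completer comparison as description only.

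For the activity monitor, recall and BSQ outcomes, state whether weeks 1 and 3 enter as visits. If they do, extend the time factor in section C.ii for those outcomes.

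The cost is a change of text: no new data and no extra visits. The protocol already plans multilevel regression for Hypothesis 2, so a related method is within its scope, and with complete data the change loses no power.

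### BMI category is a minimisation factor but is not named among the H1 ANCOVA covariates; if it is prognostic, the reported standard errors are slightly too large

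*Protocol*

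**What the plan says.** Protocol, C.ii Design, on allocation: "Participants will be blocked according to Taves minimization on gender (male vs female), BMI" (split at the 85th percentile) and baseline liking of AVGs (7 or lower against 8–10).

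Protocol, D. Statistical Analysis Plan, Major Analyses, on the repeated measures ANCOVA for Hypothesis 1: "Baseline variables, age, gender, and baseline enjoyment of AVGS will be included as control variables/ possible moderators". The moderators follow: "Moderating variables will include participant’s exercise self-efficacy, parental support for physical activity, and parental exercise self-efficacy". BMI is in neither sentence. Within section D it appears only in the list of dependent variables: "BMI/ weight loss, total energy expenditure, exercise self-efficacy".

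*Baseline variables* is not defined. Section D uses the phrase once before, under Preliminary Analyses, where it points back to age, gender, ethnicity, study condition and baseline reinforcing value. BMI is not mentioned there either.

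**The concern.** Two of the three balancing factors reappear in the H1 model by name and the third does not. Minimisation makes the arms alike on BMI category, so BMI contributes almost nothing to the sampling variation of the group difference. A model that omits BMI does not know this. It leaves the BMI variance in the residual and reports a standard error that includes it.

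With 25 children per arm, an interval that is wider than it need be is worth avoiding when the remedy is free. The undefined first item adds a second difficulty: two analysts could read the sentence and fit different covariate sets for the primary hypothesis, H1a.

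**Working it through.** **Inputs from the protocol.** 25 children per arm, 50 in total; α = 0.05, taken as two-sided because sidedness is not stated; Taves minimisation on three binary factors. The plan gives no figure on this point to reproduce, and its sample size is taken as given.

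**Assumptions, not in the protocol.** BMI category explains a share R² of outcome variance, varied from 0 to 0.30; 30% of children are above the 85th percentile.

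**1. Single outcome, no baseline adjustment.** With BMI balanced and omitted, the true variance of the group difference is (1 − R²) times the variance that the model reports. So:

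- width ratio = 1/√(1 − R²)
- true level = 2[1 − Φ(1.96/√(1 − R²))]

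At R² = 0.05: ratio 1/√0.95 = 1.026, level 0.044. At R² = 0.10: ratio 1/√0.90 = 1.054, level 0.039.

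A simulation of Taves minimisation at N = 50 (5,000 runs per setting) fitted the linear model with gender and AVG liking, with and without BMI category:

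| R² | Model SE, omitted / included | Type I error, omitted | Type I error, included |
|---|---|---|---|
| 0 | 1.00 | 0.050 | 0.051 |
| 0.02 | 1.01 | 0.049 | 0.052 |
| 0.05 | 1.03 | 0.046 | 0.051 |
| 0.10 | 1.05 | 0.038 | 0.051 |
| 0.20 | 1.12 | 0.031 | 0.054 |
| 0.30 | 1.20 | 0.020 | 0.049 |

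At R² = 0.10 the actual spread of the estimate is the same either way (empirical SD 0.2673 omitted, 0.2667 included). The mean model SE is 0.2820 omitted and 0.2674 included. So the estimate itself loses nothing; only its reported uncertainty is too large.

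Power at a standardised difference of 0.936, where 25 per arm gives about 90%: 0.900 omitted against 0.911 included at R² = 0.05, and 0.910 against 0.929 at R² = 0.10.

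**2. Outcome's baseline value in the model.** What matters now is the partial R² of BMI given baseline. Let BMI explain 10% of the outcome at both times (correlation √0.10 = 0.316) and let ρ be the baseline-to-follow-up correlation (assumed):

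- partial correlation = 0.316(1 − ρ)/√[0.90(1 − ρ²)]
- ρ = 0.5: 0.158/√0.675 = 0.192; partial R² 0.037; width 1.019
- ρ = 0.6: 0.126/√0.576 = 0.167; partial R² 0.028; width 1.014; level about 0.047
- ρ = 0.7: 0.095/√0.459 = 0.140; partial R² 0.020; width 1.010

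If BMI explains 20% and ρ = 0.6: 0.447 × 0.4/√(0.80 × 0.64) = 0.25; partial R² 0.0625; width 1.033.

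**3. Group-by-time contrast.** C.ii makes time (baseline, end of intervention, follow-up) a within-subject factor. If BMI adds the same amount to a child's outcome at every visit, that amount cancels from the within-child change and its omission costs nothing. Only a BMI effect that varies over time would matter.

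**The case against.** The strongest reply is that the covariate sentence has four items, not three, and the first, *Baseline variables*, might include BMI. That stands in part. A reader might infer that the plan excludes BMI from the model, but the text supports only that BMI is not named. The phrase does not settle the matter the other way either: its earlier use in section D does not mention BMI, and if it meant every baseline measure there would be no need to name age, gender and AVG enjoyment beside it.

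The second reply is that the harm is conditional. This stands in full. The protocol gives no relation between BMI category and reinforcing value, motivation or activity, and enrolment is limited to the 5th–95th percentile, so the upper stratum spans only the 85th to 95th. A reader might infer that precision is lost on every H1 outcome. The documents do not support that: if BMI is not prognostic, nothing is lost.

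The third reply is that figures for a single cross-sectional outcome overstate the effect in a repeated-measures analysis. This also stands for outcomes with an informative baseline, as steps 2 and 3 show. A possible exception is weekly AVG play (H1d). Entry is restricted to children who play AVGs for no more than half an hour a week, so baseline carries little information and the unadjusted figures may be nearer the mark.

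**Conclusion.** The point holds as a minor one. Allocation is balanced on BMI category, and the H1 covariate sentence neither names it nor clearly covers it. To the extent that BMI category is prognostic given the other covariates, the model standard error is somewhat too large and the test conservative.

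The size rests on assumed values:

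- about 3–5% excess interval width (level about 0.046–0.038) if BMI explains 5–10% of the outcome and baseline is not adjusted for;
- about 1–2% if BMI explains 10% and the outcome's baseline is in the model with a correlation of 0.5–0.7;
- about nil for a group-by-time contrast when the BMI effect is constant over time.

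A reader might infer that the H1 results would be biased or the tests invalid. They would not: the estimate is unbiased, type I error is not inflated, and any error is in the safe direction.

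**What to change.** In Major Analyses, add the BMI category used in the minimisation (above or below the 85th percentile) to the H1 ANCOVA covariates, beside gender and AVG liking. In the same sentence, state that *Baseline variables* means the outcome's own baseline value.

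The cost is one degree of freedom and a sentence of text. BMI category is already recorded for allocation, so no new data are needed.
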